### Recruitment {15}

We will recruit subjects from Mahidol University’s Ratchasuda College, a school dedicated to those with disabilities. Recruitment will be accomplished through a combination of announcements made at periodic seminars by local study investigators, flyers, and digital e-blasts (emails). All materials will be IRB-approved, and the curation of recruitment content will be overseen by a team of highly trained research coordinators at Mahidol University.

Forty BLV subjects will be recruited over the 5-year research timeline.

We anticipate a subject population of approximately 50% males and 50% females aged 18 and older diagnosed with visual impairment. Subjects, once identified, will be notified of the study using IRB-approved study communication.

A dedicated study research coordinator will perform screening to determine eligibility for the study and schedule the patients for enrollment and subsequent assessments at specified time points.

## Assignment of interventions: allocation

### Sequence generation {16a}

During the study’s second phase, a block randomization will be conducted, assigning participants to either group A or group B. When participants agree to participate, a number will be randomly assigned to them using Excel random number generator. Then, two randomization lists will be created using Excel random number generator, creating separate lists for group A and group B.

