Each FGD session will last roughly 60 min and include participants’ perceptions and experiences while navigating the VIS^4^ION system. The FGDs will be guided by pre-determined questions related to general perceptions of the VIS^4^ION system, as well as thoughts on the facilitators and barriers of the intervention. The FGD sessions will be audio-recorded verbatim and later transcribed and translated into English by the research team. During the sessions, the research team member will also take field notes.

#### Aim 4

A cohort of 20 (new) participants will be recruited to assess extended-use benefits over one month. We will create two groups for the randomized crossover design. Each participant will be randomized to either sequence A (10 participants) or sequence B (10 participants). During the first 15 days, group A will go through an active phase and then a passive phase for the next 15 days. Reciprocally, group B will go through a passive phase for the first 15 days and then an active phase for the second half of the month. During the passive phase, the wearable will be maintained in a monitoring mode and simply acquire data, providing no assistance/feedback on location and orientation. During the active phase, the wearable will have an activated assistive mode, i.e., the wearable will acquire data and simultaneously provide assistance/audio feedback. We will evaluate the effectiveness of the wearable for increasing navigation and quality of life. We hypothesize that the VIS^4^ION wearable will improve navigation and quality of life in individuals with visual disabilities.

During the active phase, subjects will complete their daily activities while wearing VIS^4^ION and using the mapping and localization microservice to facilitate wayfinding. Throughout the study we will monitor navigation performance through the same metrics as delineated in Aim 2 [week 2 compared to week 4], as well as to monitor for any falls that may occur (IMU-based alerting); we will also subjectively assess visual function through the 25-Item National Eye Institute Visual Function Questionnaire (VFQ25) [29], physical function and mobility, through the International Physical Activity Questionnaire (IPAQ) [30, 31], and QoL, through the World Health Organization QoL Brief (WHO-QoL-BREF) [32, 33]. The subjective assessments will be performed on day 0 (day of device delivery and initiation) and on the final day of the trial (day 31).

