### Concealment mechanism {16b}

Participants’ allocated numbers will be created by computer randomization. Sequences will only be revealed when participants are assigned, coded directly into each data file by the computer randomization.

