### Implementation {16c}

Designated team member will use the randomized list and allocate participants to groups A or B.

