## Assignment of interventions: blinding

### Who will be blinded {17a}

The study will be single-blind. Participants and a designated team member will not be blinded to the intervention. However, study team members who introduce and explain the system to each participant will be blinded and will not know if the participants are part of groups A or B. A blinded analyst will perform statistical analysis.

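### The Aim 4 allocation text names block randomisation but describes group-labelled lists that do not secure concealment, and its file coding conflicts with the blinded analyst

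*Protocol article*

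**What the plan says.** All references are to the protocol article. Aim 4 is a crossover of 20 new participants, 10 per sequence. Group A has the active mode for the first 15 days and then the passive mode; group B has the reverse order (Trial design {8} and Intervention description {11a}, Aim 4).

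- Sequence generation {16a} first states that "a block randomization will be conducted, assigning participants to either group A or group B". Each person who consents is then given a random number produced in Excel. The last step in that section reads: "two randomization lists will be created using Excel random number generator, creating separate lists for group A and group B".
- On concealment, section {16b} says: "Sequences will only be revealed when participants are assigned, coded directly into each data file by the computer randomization".
- Who applies the allocation is stated separately, in section {16c}: "Designated team member will use the randomized list and allocate participants to groups A or B".
- Section {17a}, on blinding, calls the study single-blind. Participants and a designated team member know the allocation, and the staff who introduce the system do not. It adds: "A blinded analyst will perform statistical analysis". Section {17b} says that the analyst is not meant to be unblinded. Trial design {8} calls the same study non-blinded.
- The questionnaires are given on day 0, the day the device is handed over and started, and on day 31 (Intervention description {11a}, Aim 4).

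**The concern.** The items on allocation and blinding are all filled in, so this is not a matter of detail left to a fuller document. What they state does not fit together in two places.

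First, the named method and the described method differ. A block sequence fixes, in order, whether each successive participant is A or B. A list for A and a separate list for B fix membership or order within a group. They are also labelled by group, so the person applying them can see where each entry leads. If that person also screens or takes consent, enrolment could be steered, for example by placing more confident travellers in one sequence.

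Second, writing the sequence into every data file works against a blinded analyst unless the code is masked, and no masking is stated.

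Aim 4 is the article's only randomised comparison and several of its outcomes are self-reported. What is at stake is the randomised basis of any comparison between the two sequences, such as baseline balance, period or carryover, and the stated protection from analyst knowledge.

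**Working it through.** The article gives no figure for this point, so the check sets the sections side by side. Small calculations are used for illustration only.

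**1. Can {16a} be carried out as written?** Inputs: 20 participants, 10 per sequence ({8} and {11a}). Suppose each list were drawn independently as 10 of the 20 numbers. The expected count of numbers on both lists is 10 × 10 / 20 = 5. The probability of no overlap is 1 / C(20,10) = 1/184,756. Two lists therefore work only if they are the two halves of one random split, which {16a} does not say. Section {16c} refers to a single list where {16a} has two.

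**2. Does the mechanism deliver the concealment asserted in {16b}?**

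- {16b}: the sequence is revealed only on assignment.
- {16c}: a designated team member applies the list.
- {17a}: a designated team member is unblinded; the article does not say whether this is the same person.
- Recruitment {15}: a dedicated coordinator screens. Consent {26a}: a study staff member takes consent. Neither section says that these people are different from the allocator.

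The assertion is present. The separation of roles that would support it is not.

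**3. What does an A/B code tell the analyst?** From {8} and {11a}:

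| Code | First 15 days | Next 15 days |
|---|---|---|
| A | active | passive |
| B | passive | active |

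The code and the study day together determine the mode for every record: 20 participants, both periods.

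**4. How much could be foreseen?** Someone who can read both lists knows 20 of 20 assignments. For comparison, take a proper block sequence whose block size is known to a person who sees past assignments but not the list. With a and b assignments left in the block, that person guesses the commoner one, and the expected number of correct guesses is

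E(a,b) = max(a,b)/(a+b) + [a/(a+b)]·E(a−1,b) + [b/(a+b)]·E(a,b−1), with E(0,0) = 0.

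Block of 2: E(1,1) = 0.5 + 1 = 1.5, times 10 blocks = 15.0. Block of 4: E(2,2) = 2.833, times 5 blocks = 14.2. Two blocks of 10 give 13.1 and one block of 20 gives 12.3. Chance alone gives 10. These block sizes are assumptions, since the article states none. They show why the block size should be kept from enrolling staff. They measure foreknowledge, not bias.

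**5. Day 0.** The baseline questionnaires fall on the day the device is started, and participants are unblinded. No section says whether they are completed before or after the participant learns the sequence.

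**The case against.** The strongest defence is a benign reading of {16a}: participants agree, each receives a random number, and the numbers are then split at random into list A and list B. That gives exactly 10:10, leaves no next participant to foresee if all 20 are enrolled first, and places agreement before assignment. This reading is possible, but the article does not state it. It would be a single random split and still not the block randomisation that {16a} names. Numbering after agreement is not a weakness in any case.

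Some separation of roles is already there: a coordinator screens, a designated member allocates, and the staff who explain the system are blinded. That stands. What is missing is a statement that the allocator neither screens nor takes consent.

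Three stronger readings are tempting, and the document does not support them:

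- *That allocation is known to be unconcealed.* {16b} says the opposite. The supportable statement is that concealment is asserted but not secured by the steps described.
- *That the analyst will be unblinded.* {17a} and {17b} state the contrary intent, and the code could be masked or kept out of the analyst's file. This is an unresolved conflict, not a demonstrated unblinding.
- *That baseline answers are given with the sequence known.* The order within day 0 is simply not given, and a condensed article may leave it to the full protocol. It is a risk only. Its reach is also limited: the questionnaires are taken on day 0 and day 31, when both groups have had both modes, so they supply no active-versus-passive contrast for such knowledge to distort.

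It is also fair that Aim 4 is labelled exploratory, and that the analyses listed for it in {20a} are pre/post comparisons rather than comparisons between sequences.

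**Conclusion.** Two conflicts in the text hold. Block randomisation is named, but separate group-labelled lists applied by a team member are described, so the asserted concealment lacks a mechanism that secures it. The sequence is coded into each data file while a blinded analyst is promised, and because the article defines A and B, a plain A/B code would reveal the mode in each period. Both apply to all 20 Aim 4 participants.

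The consequence is limited. The mode effect is a within-person comparison, so steered allocation would mainly damage comparisons between sequences. No size of bias can be derived from the document. The conclusion on concealment assumes that the lists carry the group label, as their description implies. The conclusion on the analyst assumes that the code written to the file is the A/B label and that this file reaches the analyst. The order of events on day 0 is a risk to close off, not an established fault. The changes are worth making because they cost little and, according to Trial status, enrolment had not begun.

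**What to change.** - **{16a}:** replace the two lists with one computer-generated A/B sequence in permuted blocks totalling 10:10, with the block size not disclosed to enrolling staff.
- **{16b} and {16c}:** have the sequence held by an existing team member who does not screen, take consent or train participants. Release each assignment only after consent and eligibility are confirmed and, as a precaution, after the day-0 questionnaires are complete.
- **{16b}, {17a} and {17b}:** keep the sequence key apart from the data files. Give the analyst masked labels for sequence (such as X/Y) and for mode (such as 1/2) until the analysis is fixed.
- **{8} and {17a}:** reconcile the non-blinded and single-blind descriptions by stating once who knows the allocation and who does not.

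The cost is protocol wording, a label-masking step when data are exported, and a short wait on day 0 between the questionnaires and the start of the assigned mode. No participants or visits are added.

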### Concealment mechanism {16b}

Participants’ allocated numbers will be created by computer randomization. Sequences will only be revealed when participants are assigned, coded directly into each data file by the computer randomization.

### Implementation {16c}

Designated team member will use the randomized list and allocate participants to groups A or B.

## Assignment of interventions: blinding

### Who will be blinded {17a}

The study will be single-blind. Participants and a designated team member will not be blinded to the intervention. However, study team members who introduce and explain the system to each participant will be blinded and will not know if the participants are part of groups A or B. A blinded analyst will perform statistical analysis.

### Procedure for unblinding if needed {17b}

Team members will be unblinded during the study period only if there are technical systems problems.

Unblinding of the data analyst is not intended.

## Data collection and management

### Plans for assessment and collection of outcomes {18a}

After each session, the collected data will be audited by a designated study team member to ensure the quality of collected data and troubleshoot any unforeseen technical issues. In addition, we will use IMU-based altering to monitor for any falls. For our subjective assessments, we will use the 25-Item National Eye Institute Visual Function Questionnaire (VFQ25) [38], the most frequently used measure of patient-reported, vision-related functioning. The NEI VFQ-25 was developed based on qualitative research with patients to measure the range of vision-related functioning experienced by persons with VI. We will use the International Physical Activity Questionnaire (IPAQ) to assess physical activity. It is a widely used self-reported questionnaire with excellent test reliability for overall score (ICC = 0.81) and physical activity (ICC = 0.84–1.00) [30]. We will administer the World Health Organization QoL Brief (WHO-QoL-BREF) to assess and compare the quality of life. WHO-QoL-BREF is 26 items, self-reported questionnaires that address 4 domains of quality of life, including physical health, psychological health, social relationships, and environments. This test was developed collaboratively and field-tested across several cultural contexts, therefore it is highly recommended to study outcomes and/or measure the quality of life [32, 33].

### Plans to promote participant retention and complete follow-up {18b}

A research coordinator at Ratschasuda College will coordinate study assessments while the investigative team will maintain open channels of communication between relevant study facilities for any query at any time point. A clear division of labor and frequent communication will ensure that we retain subjects in the study.

### Data management {19}

All data management activities will be rigorously and directly supervised and monitored by the PI and Co-PI. All computerized data files will be de-identified and will not contain any information that could be used to identify individual subjects. Rather, data files will be assigned a unique alphanumeric identifier. The code key connecting the data with the subjects’ names will be kept in a separate, secure location. Data will be backed up to a secure research drive. Only the PI and co-investigators will be able to access the data.

### Confidentiality {27}

Confidentiality of research records will be strictly maintained. All computerized data files will be de-identified and will not contain any information that could be used to identify individual subjects. Rather, data files will be assigned a unique alphanumeric identifier. The code key connecting the data with the subjects’ names will be kept in a separate, secure location. Data will be backed up to a secure research drive. Only the PI and coinvestigators will be able to access the data.

The results of these experiments may be published (book or journal) or used for teaching purposes. The identities of participants and participants’ family members will not be revealed in any publication or teaching material without specific permission. After publication, the data may be removed from the PI’s computers and file servers.

The PI will promptly report all adverse reactions to the IRB. An annual report on data and safety monitoring will be submitted to the IRB. This report will detail any adverse events.

### Plans for collection, laboratory evaluation, and storage of biological specimens for genetic or molecular analysis in this trial/future use {33}

Not applicable; the study does not involve biological specimens.

## Statistical methods

### Statistical methods for primary and secondary outcomes {20a}

#### Aim 1

We expect that mapping based on the mapping microservice (Map-Net) will demonstrate sub-meter level distance accuracy, orientation accuracy of < 5 degrees, and good precision. Our tests of mapping performance will include:Multiple correlations of actual to inferred 3D position/orientation (goodness of fit metric), please see Fig. 4aAverage error as a function of distance from the center of the 3D map, please see Fig. 4bEfficiency targets (coverage: 1 block/pedestrian hour of mapping; data storage: 1 block of image data = 200 Mb)

**Fig. 4 Fig4:**
[figure not shown]
Correlations between ground truth positions and those computed from Pos-Net and Loc-Net (left) and corresponding 2D errors (right)

We have collected a small sample of preliminary data (Fig. 4) to demonstrate the feasibility of these analyses, and that they are capable of demonstrating improvement (green; Loc-Net) relative to our baseline (blue; prior art) methods. There is a clear, qualitative improvement in the green plots, both in precision (left, improved correlation) and accuracy (right, error scatter). Our ability to discriminate between methods will only improve with the larger dataset proposed for this aim.

#### Aim 2

We will use the trained network to predict the real-time pose of a BLV user and create a mobility home range for each participant during both the passive and active phases of this initial pilot. We anticipate that route planning will improve through more efficient wayfinding in the active phase, when users have a more comprehensive understanding of the local environment (spatial cognition). We will extract paths between pre-selected pairs of locations during the active and passive phases (e.g., residence to classroom building) traversed in the pre (first 5 days) and post (last 5 days) periods to evaluate our predictions, measuring:Average changes and variability in path length (i.e., percent change in path length [difference test based on binomial distribution] and path variance [F-test of variances])Average changes in normalized traversal time (i.e., percent change in time [difference test based on binomial)For destinations that denote social activities, estimate the difference in time spent on such activities pre to post [time difference based on Wilcoxon signed rank test].Pre vs. post fall rates using an exponential waiting-time model of time between falls [Poisson rate of falling]Total area covered on an hourly, daily, and weekly basis to assess a home range

#### Aim 3

We will perform a content analysis of the transcripts and notes using NVIVO software [36]. Specific quotations, group interactions, and observations will be assigned codes based on content. The following are the core acceptability and appropriateness outcomes that will be assessed: (a) satisfaction or agreeability with the refined intervention design; (b) perceptions on how the intervention can be adopted within their setting; (c) perceived willingness or interest to participate; and d) perceived relevance and fit of the intervention for the setting. Significant inductive (emerging) codes will also be identified, assessing for differences by sex. Coded items will be grouped into a hierarchical, branching structure in which broad concepts are first identified. The themes and interpretive ideas emerging from those constructs are labeled using constant comparison techniques and subsequently synthesized using matrices structured by the main themes of the analysis [39, 40]. In addition, we will measure acceptability, feasibility, and appropriateness as lumped average scores (5-point Likert scale) across a 27-question post-interview questionnaire. Averages of > 2.5 will indicate an overall positive rating on each dimension, although low average scores on individual questions within each dimension (i.e., non-lumped) will be used to aid product development.

#### Aim 4

We will evaluate the effectiveness of our approach to increase efficient mobility among BLV students, as well as health and well-being. Descriptive statistics will be generated for quantitative data, and thematic content analysis will be performed for qualitative data. We will perform a content analysis of the transcripts and notes using NVIVO software [36], in a manner similar to what has been described above in Aim 3. Results will be categorized according to the seven dimensions of the Saunders Framework: fidelity, dose delivered, dose received (exposure), dose received (satisfaction), recruitment, reach, and context. Formative data will be reported iteratively to the study team throughout the trial, in order to improve intervention delivery, while summary data will be reported at the end of the trial along with the results of the trial. We will compare pre/post-differences in subjective assessments and in navigation and health metrics.

We will compare pre-post metrics using Bayesian model comparison techniques. For example, we will compare fall rates using an exponential waiting-time model of duration between falls (Poisson rate of falling,) based on the ratio (Fig. 5):

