### Sample size [1]

A total of 40 visually impaired subjects will be recruited over the 5 years of this proposed research program. In the first phase, we will focus on demonstrating that travel has improved, using a metric based on the ratio of path length. Path length is a non-normal variate, right-skewed, and must be transformed to satisfy the constraints of a parametric statistical test.

We use log-transformed path-length ratios for the power calculation, by which we determined that, with a statistical power of at least 0.8, we will be able to detect a path-length difference for 20 subjects in which the initial path lengths are 40% shorter than those taken when using the navigation aid, assuming a standard deviation of length-ratios no larger than 2.5.

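### The Aim 2 tests for path length and traversal time do not match the log-ratio scale on which the trial is powered: the F-test ignores pairing and skew, and the binomial test is ambiguous and weak

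*Protocol article*

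**What the plan says.** In the protocol article, Statistical methods {20a}, Aim 2, each participant's paths between chosen pairs of locations are compared between the passive and the active days, that is, paths "traversed in the pre (first 5 days) and post (last 5 days) periods to evaluate our predictions". The tests are named in brackets:

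- Path length: "percent change in path length [difference test based on binomial distribution] and path variance [F-test of variances".
- Traversal time: "percent change in time [difference test based on binomial".
- Time at social destinations: "time difference based on Wilcoxon signed rank test".

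The section mentions no transformation. Only the third test is recognisably paired.

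The Sample size section treats the same metric differently: "Path length is a non-normal variate, right-skewed, and must be transformed to satisfy the constraints of a parametric statistical test". It continues: "We use log-transformed path-length ratios for the power calculation". The planning inputs are 20 subjects, power of at least 0.8, a length-ratio standard deviation of at most 2.5, and an effect in which "initial path lengths are 40% shorter than those taken when using the navigation aid".

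**The concern.** One section requires a transformation and sets the sample size on log ratios. The other names tests that do not use that scale. This is not a detail left open for an analysis plan, because the tests are named.

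Two things are at stake.

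- **Variability.** The F-test refers the ratio of two sample variances to an F distribution. That requires the samples to be independent and normal. Pairing breaks the first condition and skew breaks the second. The two faults push the error rate in opposite directions, so a reader cannot tell whether a reported change in path variance is credible.
- **Average change in length and time.** Percent change is continuous, so a binomial test can only act on a dichotomy such as shorter versus longer. That does not address the quantity the protocol says it will measure, an average change, and it loses power in a trial of 20 people.

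**Working it through.** **Inputs from the protocol.** n = 20 participants, each contributing both phases. The 40% difference is a ratio of 0.6, so the effect is |ln 0.6| = 0.511; its direction does not affect a two-sided calculation. The SD of 2.5 has no stated scale and is read here as ln 2.5 = 0.916 on the log scale. Alpha and sidedness are not given in the power statement; 0.05 is assumed.

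**1. The protocol's own figure.** Standardised effect d = 0.511/0.916 = 0.557, and d√20 = 2.493.

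- One-sided normal approximation: Φ(2.493 − 1.645) = 0.802. This reproduces the stated 0.80.
- Two-sided normal approximation: Φ(2.493 − 1.960) = 0.703.
- Paired t-test (noncentral t, 19 df): 0.776 one-sided, 0.658 two-sided.
- If 2.5 is taken directly as the log-scale SD, d = 0.511/2.5 = 0.204 and power is 0.14 to 0.23.

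So 0.80 is reached only with a one-sided normal approximation and SD = ln 2.5.

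**2. The binomial test as a per-participant sign test.** On the same inputs, the chance that a participant changes in the expected direction is Φ(0.557) = 0.711. A two-sided test at 0.05 rejects at 15 or more of 20 in one direction. Its exact level is 2 × P(X ≥ 15 | 20, 0.5) = 2 × 0.0207 = 0.041. Power is P(X ≥ 15 | 20, 0.711) = 0.46. The paired t-test on log ratios has 0.66, and a simulated Wilcoxon signed rank test 0.64.

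If signs were instead counted per trip as though independent, the simulated type I error is 0.11 to 0.17 with 5 trips per person and 0.22 to 0.30 with 10, at an assumed intraclass correlation of 0.3 to 0.5. The text does not say which unit is meant.

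**3. The F-test.** Simulation: 50,000 runs per setting, 20 pairs, lognormal lengths, one length per person per phase, identical distributions in both phases, nominal two-sided 5%. Log SDs and correlations are assumptions, because the protocol gives none.

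| Scale | Log SD | Correlation 0 | Correlation 0.5 |
|---|---|---|---|
| Raw | 0.3 | 11.5% | 6.9% |
| Raw | 0.5 | 22% | 15% |
| Raw | 0.65 | 31% | 24% |
| Logged | any of these | about 5% | 2.6% |

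Higher correlation pulls the rate down on either scale. Logged lengths give about 0.3% at correlation 0.8. Raw lengths at correlation 0.9 give 0.1% (log SD 0.3) and 3.0% (log SD 0.65). The Pitman-Morgan paired variance test on log lengths stayed between 4.8% and 5.2% in the settings tried.

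**4. The summary measure.** If individual percent changes are averaged and the median ratio is 1, the expected average is exp(s²/2) − 1, where s is the SD of the log ratio. This is +2% at s = 0.2, +13% at s = 0.5 and +52% at s = 0.916.

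**The case against.** **The binomial test can be sound.** A sign test is a binomial-based test of difference. With one sign per participant it is valid for paired data however skewed, and a distribution-free test is a defensible choice in a small pilot. This stands. A reader might infer that the binomial p-values must be wrong, but the protocol does not support that. The defects are an undefined unit, a target other than average change, and lost power.

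**The transformation could be carried over.** The Sample size section demands it for parametric tests, and the F-test is one. This is a fair reading, and on it the inflated rates fall away. It does not rescue the test: ignoring the pairing then makes it conservative, increasingly so as the correlation between phases rises.

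**The tests do not bias the estimate.** This also stands. One might infer from the skew that the named tests distort the average percent change, but the choice of test leaves the estimate alone. The upward pull in step 4 comes from averaging raw percent changes, and the protocol does not say whether it averages individual changes or compares mean lengths. The +52% is the top of an assumed range, and 2.5 is stated as an upper limit.

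**A variance difference after a shift in length is real.** If every path shortened by 40% with the same relative variability, raw variance would fall to 0.6² = 0.36 of its former value. An F-test that detects this is not giving a false positive, so that scenario is no evidence of a wrong error rate.

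**The unit is assumed.** Several location pairs over five days per phase could make path variance a matter of repeated traversals. The simulated rates are therefore illustrative.

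**Conclusion.** The point holds in a limited form. The Aim 2 tests are inconsistent with the protocol's own statement about skew, transformation and the log-ratio scale.

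The F-test of variances is the clearest fault. Its conditions are not met, and its actual error rate can lie well above or well below 5%, depending on scale and correlation. The direction of the error for each reading is secure. The exact rates depend on lognormal lengths, one value per person per phase, and the assumed log SDs and correlations.

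For length and time, the binomial label is ambiguous. On its most favourable reading it gives valid p-values with power of about 0.46. The two-sided log-ratio t-test gives 0.66, so changing the test recovers power but does not reach the stated 0.80. These power figures rest on reading the SD as ln 2.5 and on a two-sided 0.05 level.

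**What to change.** Replace the bracketed tests in Statistical methods {20a}, Aim 2:

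- **Path length and traversal time.** Take each participant's mean log(active/passive) over location pairs and use a paired t-test. Alternatively, fit a mixed model to log values with participant and location-pair effects. Report the geometric mean ratio with a 95% CI. This matches the scale of the power calculation and avoids the upward pull of averaging raw percent changes.
- **Variability.** Replace the F-test with the Pitman-Morgan test on log path lengths, or estimate phase-specific residual variances in the same mixed model.
- **If a sign test is kept**, say so, state that it uses one sign per participant, and present it as supportive.

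The Sample size section should also state alpha, sidedness and the scale of the SD, so that the power can be matched to the test used.

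The cost is a few lines of wording and no new data. Trial status reports that enrolment had not begun, so the protocol as written allowed the change before any data were seen.
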